### Data processing & cleaning

In this section we describe how we handle outliers, missing data, and model specification. Firstly, given the presence of by-item and by-participant slopes and intercepts, outliers are less likely to be problematic for the analysis. However, as an additional check, using the *extremes* command on STATA for all numeric outcomes (i.e., fluency measures) we will initially check for cases with extremely high or low values. If any extreme values are identified, they will be investigated further by checking their residuals and leverage. A sensitivity analysis will be conducted to determine whether outlier data will be included or excluded in the analysis. If results are heavily affected by the inclusion of an outlier (and there is no evidence to suggest that differences in results are not random) then this data will be excluded from the analysis.

Secondly, if there is more than 5% of the data missing, this will be further investigated to check if by-item attrition is systematic or randomly distributed. If it is randomly distributed, then these missing observations are automatically removed by STATA in analysis. However, if the missing observations are systematic (e.g., most of the missing data is in response to one particular occupation or stimuli) then this will be investigated further and potentially dropped from the analysis.

Finally, to avoid an overspecification of the models, models that include interactions as predictors will be compared to a simplified model that excludes these interactions using the Bayesian Information Criterion (BIC). The BIC will be used to determine if the unrestricted or restricted model is a better fit for the data.

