### Outcomes of interest

To answer the research questions outlined above, the study focuses on two outcome categories: fluency measures and the participant’s gender interpretation of the prime.

Fluency measures consist of 5 dependent variables: the total number of words produced, hesitation markers, number of false starts, fluency mistakes, and initial response time. These measures are consistent with current literature on speech production [34]. The focus on fluency allows for exploration of processing costs and benefits due to in/congruent or asymmetric stimuli. Additionally, fluency measures help show what is easily accessed or recalled. Processing benefits are expected when participants’ S-gender expectations are not violated (i.e., a *secretary* in feminine morphology and a *manager* in masculine morphology compared to a *secretary* in the masculine). Importantly however, roles associated with women presented in masculine morphology should *not* result in processing costs if masculine G-gender is truly interpreted as generic or unmarked.

To measure the participant’s interpretation of the prime their responses will be coded based on the proportion of gendered morphosyntactic markers in their speech. Importantly, this will be weighted at the tensed phrase (TP) level. This is to avoid inflating scores based on morphosyntactic markers for the sake of agreement across noun phrases or verb phrases. This coding will be used to derive two other categorical variables to be used in the analysis: the participant’s gender expectations and whether the expectations are congruent with the social stereotype associated with the prime.

Example 3 provides a fictitious response to the stimulus “*manager [+masc]*” and how this would be coded. Firstly, we can see that there are three morphosyntactic markers that are masculine, two of which are used only for agreement purposes. Secondly, we can determine that the participant interpreted the stimulus to be a man and that this response is congruent with the prime (i.e., grammatical gender and social gender are not asymmetric).

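### The outlier rule can exclude valid fluency data because they influence the result, and it lets a sensitivity analysis choose the primary data set

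*Protocol article*

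**What the plan says.** The rule is in the protocol article, under Data processing & cleaning. It applies to the numeric outcomes, which the protocol equates with the fluency measures. Outcomes of interest lists these as "the total number of words produced, hesitation markers, number of false starts, fluency mistakes, and initial response time".

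The steps are:

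1. Screening: "we will initially check for cases with extremely high or low values".
2. Follow-up of any extreme values: "they will be investigated further by checking their residuals and leverage".
3. Decision: "A sensitivity analysis will be conducted to determine whether outlier data will be included or excluded in the analysis".
4. Trigger: "If results are heavily affected by the inclusion of an outlier", subject to a bracketed condition that nothing suggests the difference in results is other than random.
5. Consequence: "then this data will be excluded from the analysis".

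The section opens with the view that, because the models have random slopes and intercepts, "outliers are less likely to be problematic for the analysis". It gives no cut-off for an extreme value or for a heavy effect, and no standard for the evidence in the bracket. It does not ask whether the value came from a recording, prompt or task fault.

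**The concern.** The criterion for removal is the effect on the result, not the validity of the observation. Residuals and leverage describe how unusual or influential a point is; they do not show that it is wrong. The bracketed condition allows an influential value to stay, but sets no standard for when. A sensitivity analysis normally shows how far a fixed primary result depends on a choice. Here it makes the choice.

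This matters most for research question 1c. The Hypotheses section predicts slower and less fluent responses where grammatical and stereotype cues conflict. A long delay or a very low word count on an incongruent prompt may therefore be the effect under study. Removing it because it moves the estimate can shrink that effect.

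The second problem is discretion. The comparison requires both fits to be seen before the data set is settled. The Procedure blinds the researcher to block allocation, but the protocol does not say that this covers the outlier decision, and a fitted model contains the language condition.

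**Working it through.** **Figures in the plan.** The outlier rule has no figure attached. The sample size reproduces: 4 × 30 + 30 + 30 = 180.

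**Number of trials exposed.** From Table 2, count the strictly masculine or strictly feminine forms of the male- and female-stereotype nouns:

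- Block 1: 4 congruent, 2 incongruent
- Block 2: 2 congruent, 3 incongruent
- Block 3: 2 congruent, 3 incongruent

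That is 8 congruent and 8 incongruent cells. At 30 participants per block (Sample size), 8 × 30 = 240 trials of each kind.

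**Simulation assumptions (not from the documents).** Initial response time is log-normal with log mean 0.3 and log SD 0.6. Values more than 3 SD from the mean are flagged and all are dropped. The test is a two-sample t-test at 5%, a simplification of the planned mixed model. The cost is the mean incongruent time minus the mean congruent time, and loss = 1 − (cost after exclusion ÷ cost before).

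| How the cost arises | Cost before, s | Cost after, s | Loss | Power before | Power after |
|---|---|---|---|---|---|
| Uniform slowing, 0.20 s | 0.198 | 0.189 | 5% | 0.53 | 0.65 |
| Uniform slowing, 0.25 s | 0.252 | 0.239 | 5% | 0.75 | 0.85 |
| 0.20 s plus 3% stray 5 s delays in both arms | 0.200 | 0.182 | 9% | 0.36 | 0.51 |
| Proportional slowing, +0.15 on the log scale | 0.263 | 0.212 | 19% | 0.71 | 0.68 |
| 5% of incongruent trials delayed by 5 s, nothing else | 0.25 | 0.04 | 84% | 0.57 | 0.09 |

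The 5 s delay lies inside the 20-second window given under What is the task?. Repeat runs of the last row gave power before exclusion of 0.54 to 0.57.

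**The bracketed condition.** In the last row, flagged values average 2.0 congruent against 11.8 incongruent, and a Fisher test on those counts is significant in 73% of runs. If that test counts as evidence of non-randomness and the values are then kept, about 0.21 s of the cost remains: 1 − 0.21/0.25 = 16% loss.

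**Type I error with no true effect.**

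- All data kept: 5.0% at nominal 5%, 9.7% at nominal 10%.
- Flagged values always dropped: 4.9% and 9.7%.
- Whichever fit is significant is kept: 7.5% and 14.4%. A repeat gave 7.6% and 15.6%.

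**A second set-up.** This used the Table 2 layout with participant and item effects, a 1.5 × IQR flag, alpha 0.10, and a heavy effect defined as a shift above 20% or a flip in significance. With long delays in 4% of congruent and 10% of incongruent trials, the cost fell from 0.23 s to 0.02 s and power from 47% to 13%. Adding a 0.1 s general shift, it fell from 0.34 s to 0.12 s. With no effect, the rule applied in both directions rejected in 8.5% to 9.4% of runs.

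**The case against.** Several stronger readings are tempting, and the document does not support them.

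- **Exclusions follow the answer the analyst wants.** A reader might infer this from the missing threshold. The text names no direction: a value is open to exclusion whether it helps or hurts the hypothesis. Inflated type I error describes a misuse that the wording permits, not the rule as written.
- **Most of a real cost will be deleted.** That requires a cost consisting only of rare long delays, with every flagged value dropped and the bracket ignored. The Hypotheses section predicts slower responses in general and does not confine the cost to extremes. Under uniform slowing the loss is about 5% and exclusion improves power.
- **The bracket is always satisfied, so exclusion is the norm.** This is an interpretation. An imbalance of flagged values between conditions could count as contrary evidence. What stands is that the standard is unstated.
- **The whole study is affected.** The rule covers numeric fluency outcomes only. The gender-interpretation outcomes, which serve questions 1a, 1b and 2, are not touched. Only response time was simulated; the other four fluency measures are not times.

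It is also fair to say that a condensed article may leave numeric cut-offs and the reporting of both fits to a fuller plan. Their absence is not the point. The criterion itself is stated, under a heading that calls the plan pre-specified, and adding a cut-off for influence would not turn it into a test of validity.

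**Conclusion.** The concern holds, limited to the fluency outcomes and mainly to question 1c. The rule makes removal depend on influence, without a fault requirement or threshold, and uses a sensitivity analysis to select the primary data set. It can therefore discard valid observations that carry the hypothesised cost, and it leaves a choice between two fits after both are seen.

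The attenuation ranges from about 5% (uniform slowing, with a gain in power) through about 20% (proportional slowing) to about 84% in the worst case. These sizes rest on the assumed response-time distribution, the 3-SD flag and the form of the cost, none of which the protocol gives. Symmetric use leaves type I error at its nominal level; the rise to about 7.5% (about 14.5% at the 10% level) needs an analyst who keeps the significant fit.

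**What to change.** Replace the exclusion rule for the fluency outcomes with three statements:

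1. The primary analysis keeps every valid trial.
2. A trial is excluded only for a recording, prompt or task fault from a list fixed in advance, judged without sight of language condition or model results.
3. The fit without extreme values is reported beside the primary as a sensitivity analysis and does not replace it.

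The residual and leverage checks can stay as diagnostics. Analysing response time on the log scale is optional and not part of this fix, since it changes the quantity estimated.

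The cost is one paragraph of analysis-plan wording. The downside is somewhat wider intervals, and possibly lower power, when stray extremes are present: in the simulated case with stray delays in both arms, keeping all data gave power 0.36 against 0.51 after exclusion.

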### Design

The experiment employs both between and within variation and is randomised through a block design (5 blocks). The first factor, which varies between participants, is the language condition. There are four main language conditions, and one sub-condition: singular masculine generics, singular feminine g- gender, gender inclusive binomial word-pairs, English gender neutral, and plural masculine generics as the sub-condition (see Table 1).

**Table 1 pone.0292936.t001:** Between variation and breakdown of conditions.

Condition		Example
**1.**	Singular generic masculine	مدرس ‘Teacher[+masc]’
**1.1**	Plural generic masculine	مدرسين ‘Teachers[+masc]’
**2**	Singular feminine	مدرسة ‘Teacher[+fem]’
**3**	Gender-inclusive: Feminine/Masculine word-pair	مدرسة/ مدرس ‘Teacher[+fem]/Teacher[+masc]’
**4**	Gender-neutral: English neutral	Teacher

There is one factor that varies within-participant and that is the ‘stereotypicality’ of the role. Role nouns can be associated with men (e.g., *manager*), associated with women (e.g., *nurse*), or neutral (e.g., *student*). All participants are presented with the same 12 role nouns (4 in each stereotype) but in different language conditions.

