**Fig 1 pone.0292936.g001:**
[figure not shown]
Condition allocation based on participants’ characteristics.

The first component evaluates the effect of Arabic grammatical gender (in the singular) on occupational expectations amongst Egyptian Arabic speakers. In this component, participants are randomly allocated across blocks 1–3 where they are presented with role nouns that vary by language and stereotype condition through a Latin square (see Table 2). Based on this design, 3 different participants are required to complete an observation for one role noun (e.g., *nurse*) in the masculine, feminine, and word-pair conditions. There are several reasons for this choice; firstly, it reduces the chance that participants develop an intuition about the real purpose of the experiment. Secondly, it prevents participants from anticipating the G-gender of the stimuli. Thirdly, this design helps avoid responses that are strictly based on priming patterns and local syntactic consistency [32].

**Table 2 pone.0292936.t002:** Latin square blocks for the singular Arabic conditions.

Block	Male Stereotype	Female Stereotype	No Stereotype
**Block 1**	مدير Manager [+ masc]	ممرضة Nurse [+ fem]	تلميذة/تلميذ Student [+ fem/masc]
	مهندسة/مهندس Engineer [+ fem/masc]	راقص Dancer [+ masc]	مغنية Singer [+ fem]
	محامية Lawyer [+ fem]	مضيفة/مضيف طيران Flight Attendant [+ fem/masc]	ممثل Actor [+ masc]
	دكتور Doctor [+ masc]	عاملة نظافة Cleaner [+ fem]	مسؤولة / مسؤول مبيعات Salesperson [+ fem/masc]
**Block 2**	مديرة/مدير Manager [+ fem/masc]	ممرض Nurse [+ masc]	تلميذة Student [+ fem]
	مهندسة Engineer [+ fem]	راقصة/راقص Dancer [+ fem/masc]	مغني Singer [+ masc]
	محامي Lawyer [+ masc]	مضيفة طيران Flight Attendant [+ fem]	ممثلة/ممثل Actor [+ fem/masc]
	دكتورة / دكتور Doctor [+ fem/masc]	عامل نظافة Cleaner [+masc]	مسؤولة مبيعات Salesperson [+ fem]
**Block 3**	مديرة Manager [+ fem]	ممرضة/ممرض Nurse [+ fem/masc]	تلميذ Student [+ masc]
	مهندس Engineer [+ masc]	راقصة Dancer [+ fem]	مغنية/مغني Singer [+ fem/masc]
	محامية/محامي Lawyer [+ fem/masc]	مضيف طيران Flight Attendant [+ masc]	ممثلة Actor [+ fem]
	دكتورة Doctor [+ fem]	عاملة/عامل نظافة Cleaner [+ fem/masc]	مسؤول مبيعات Salesperson [+ masc]

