#### Exclusion criteria

Participants not sufficiently proficient in English (for the English Condition) or Arabic (for the Arabic conditions) will be excluded from the analysis. Proficiency will be determined using a C-test, and results below native-level proficiency will be excluded (this corresponds to a score of less than 90% on the test). Additionally, participants that are aware of the purpose of the experiment, based on their responses in the exit survey, will be excluded. Finally, participants that repeatedly or purposely ignore the two key tasks (pressing spacebar and producing speech) for more than 2 occupations will be excluded.

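### Missing trials are checked by noun and only above 5% overall, an axis on which the Latin square hides condition-driven non-response; deleting silent trials can then shrink the response-time contrast

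*Protocol article*

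**What the plan says.** The missing-data rule is in the Protocol article under Data processing & cleaning. It applies "if there is more than 5% of the data missing", and then "this will be further investigated to check if by-item attrition is systematic or randomly distributed". The next step is fixed: "If it is randomly distributed, then these missing observations are automatically removed by STATA in analysis". The only pattern offered as systematic is that "most of the missing data is in response to one particular occupation or stimuli"; such data are investigated and may also be dropped. The section names no check by language condition, by congruity or by block.

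Under Conditions, blocks 1–3 follow a Latin square (Table 2), so that "3 different participants are required to complete an observation for one role noun (e.g., *nurse*) in the masculine, feminine, and word-pair conditions". Under Design, "All participants are presented with the same 12 role nouns (4 in each stereotype) but in different language conditions".

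Exclusion criteria adds a participant-level rule: people who repeatedly or deliberately disregard the spacebar and speech tasks "for more than 2 occupations will be excluded".

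The Hypotheses section expects processing costs for incongruent prompts, for the feminine condition overall, and possibly for word-pairs. Initial response time is one of the five fluency outcomes, and the prompt stays on screen for 20 s.

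**The concern.** The predicted costs lie along language condition and language × stereotype. The missing-data check looks along occupation. A Latin square exists to make occupation orthogonal to language condition, so the plan checks for informative loss on the axis that the design has cleared of it, and only once the overall loss passes 5%.

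This matters most for question 1c, which asks whether conflicting cues carry a processing cost. A participant who says nothing before the prompt disappears has no observed initial response time, and the true latency lies beyond the window. If difficult prompts produce more such trials, deletion removes the slowest responses, and more of them from the difficult cells.

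**Working it through.** **Inputs from the article.** 30 participants in each of blocks 1–4, plus 30 bilinguals and 30 monolinguals in block 5: 4 × 30 + 30 + 30 = 180, as stated. Blocks 1–3 give 90 × 12 = 1080 trials, which is 90 per noun and 360 per language condition. All non-response rates below are assumptions.

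**1. Balance of Table 2.** Each of the 12 nouns appears exactly once as masculine, feminine and word-pair, and each block has 4/4/4. Counting only the stereotyped nouns in a single gender:

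| Block | Congruent | Incongruent |
|---|---|---|
| 1 | 4 | 2 |
| 2 | 2 | 3 |
| 3 | 2 | 3 |

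Incongruent cells: 2 + 3 + 3 = 8 of 36.

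**2. Expected rate per noun.**
- Driven by language condition: every noun has (p_masc + p_pair + p_fem)/3. With 4/8/12% that is 24/3 = 8.0% for all 12 nouns.
- Driven by incongruence (rate q in incongruent cells, r elsewhere): a stereotyped noun has (q + 2r)/3 and a neutral noun has r. With 15% and 4%: (15 + 8)/3 = 7.67% against 4.0%. The eight stereotyped nouns look alike; the four neutral nouns are lower.

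**3. Detection.** Simulated chi-square tests at 0.05, blocks 1–3, 4000 replicates:

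| Assumed non-response | Overall | By item | By design factor |
|---|---|---|---|
| masc/pair/fem 4/8/12% | 8.0% | 4% | 96% (condition) |
| masc/pair/fem 3/3/15% | 7.0% | 4% | 100% (condition) |
| incongruent 15%, else 4% | 6.4% | 25% | 99% (condition × stereotype) |
| incongruent 20%, else 3% | 6.8% | 63% | 100% (condition × stereotype) |

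In the first two rows the by-item test performs no better than its own 5% error rate. In no replicate did most of the missing data fall on one noun or stimulus, the article's only example.

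**4. The 5% trigger.** Overall loss over the 36 cells is (8q + 28r)/36. Setting this at or below 5% gives q ≤ (1.80 − 28r)/8.
- r = 0: q up to 22.5%
- r = 1%: q up to 19%
- r = 3%: q up to 12%

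Loss confined to the feminine condition (12 of 36 cells) can reach 0.05 × 36/12 = 15%. With q = 12% and r = 1%, overall loss is (0.96 + 0.28)/36 = 3.4%, and the check would start in about 0.2% of simulated studies.

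**5. Direction of bias for response time.** Take latency as normal on some scale, with the window limit k SD above the congruent mean and a true cost of d SD. After deletion the observed difference is d − [λ(k − d) − λ(k)], where λ(x) = φ(x)/Φ(x).

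| k | Lost, congruent | d | Lost, incongruent | Observed difference | Shrinkage |
|---|---|---|---|---|---|
| 1.5 | 6.7% | 0.25 | 10.6% | 0.25 − (0.204 − 0.139) = 0.185 | 26% |
| 1.5 | 6.7% | 0.50 | 15.9% | 0.50 − (0.288 − 0.139) = 0.351 | 30% |
| 2.5 | 0.6% | 0.25 | 1.2% | 0.25 − (0.032 − 0.018) = 0.236 | 6% |
| 2.5 | 0.6% | 0.50 | 2.3% | 0.50 − (0.055 − 0.018) = 0.462 | 8% |

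The contrast moves towards zero in every row. The amount depends on how often people are silent.

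**The case against.** Several stronger readings are tempting, and the article does not support them.

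- **That the by-item check is blind to loss from incongruence.** It is not. Neutral nouns are spared, so gendered and neutral nouns differ. With 12% against 1%, a by-item test would flag the pattern in about 47% of simulated studies and a gendered-versus-neutral comparison in about 95%, if the check were run at all. Exact evenness holds only for a language-condition effect in blocks 1–3. Block 4 is unbalanced: including it under 4/8/12%, with plural masculine at 4%, gives 7–9% by noun.
- **That anyone silent on three nouns is excluded.** The rule concerns people who repeatedly or deliberately disregard the tasks, and involuntary silence is not clearly that. Even if silence counted, 12% and 1% with independent trials would exclude 0.24% of block 1 and 0.60% of blocks 2–3: about 0.07 of 30 and 0.36 of 60 people. Clustering within people would raise this.
- **That setting silent trials to 20 s measures the bias.** Assume 5% against 1% silence, a 2.0 s base and a 0.5 s cost among responders. The difference becomes (0.95 × 2.5 + 0.05 × 20) − (0.99 × 2.0 + 0.01 × 20) = 1.2 s. But complete-case analysis recovers the 0.5 s that was put in; the 1.2 s answers a different question.
- **That deletion always biases.** If loss depended only on language condition and stereotype, and both were modelled, deletion would cost precision without by itself biasing the contrast. Bias needs dependence on the unseen value, which holds for a latency cut off by the window.

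Other points on that side also stand. Four of the five fluency outcomes are counts that may already be scored 0 for silence. The one-occupation pattern is only an example, and a stimulus may mean a noun in one form. Low-frequency nouns were screened out, output is rewarded, and the pilot may lengthen the window. Silence may be rare.

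**Conclusion.** The point holds in a limited form. The rule uses the wrong axis and a threshold that can conceal large losses in the cells of interest. In blocks 1–3 a by-item check has no power against non-response driven by language condition, and only weak power (25–63% in the assumed scenarios) against non-response driven by incongruence. Concentrated loss of up to 22.5% in the incongruent cells, or 15% in the feminine condition, does not pass the 5% trigger if nothing is lost elsewhere.

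The consequence is firmest for initial response time, where deleting silent trials selects on the outcome and can shrink the question 1c contrast. Its size cannot be fixed from the article; the 6–30% range above is illustrative and rests on assumed normality and silence rates. For word counts the concern applies only if silence is coded as missing, which the article does not say.

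**What to change.** In Data processing & cleaning:

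1. Tabulate and compare missing trials by language × stereotype cell and by block, whatever the overall percentage, and keep the by-item table beside it.
2. State that a silent trial counts as 0 words.
3. Analyse initial response time as right-censored at the trial limit, at least as a sensitivity analysis next to the planned linear mixed model.
4. Report the main results with and without participants removed under the rule on more than two occupations, because blocks 1, 2 and 3 hold 2, 3 and 3 incongruent prompts per person.

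The cost is a few tables, one censored-time model and one repeat analysis, with no new data. Some trials from inattentive participants will stay in those analyses, at a small loss of precision.
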